#### 2.6.2. Secondary outcome measures.

##### 2.6.2.1. TCM symptom score.

The form of TCM symptom will be measured at the baseline, after 5 weeks of treatment.

##### 2.6.2.2. Reproductive hormone.

Blood sampling test of β-HCG, estradiol (E2), progesterone (P) levels will be measured once a week after embryo implantation, and additional tests should be conducted at any time according to the clinical needs.

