### 2.5. Interventions

The randomization strategy will be used to divide the participants into one of the 2 groups.

The treatment group: conventional western medicine after embryo transplantation combined with Jian-Pi-An-Tai formula. Jian-Pi-An-Tai formula is composed of codonopsis pilosula, astragalus membranaceus, fried atractylodes macrocephala, donkey hide gelatin, mulberry parasitic, dodder seed, raw rehmannia root, cooked rehmannia root, ramie root, scutellaria baicalensis, paeony root, wolfberry fruit, eclipta alba, perilla frutescens stem, licorice root, and dipsacus, which provided by Preparation Center of the Hangzhou TCM Hospital Affiliated to Zhejiang Chinese Medical University. The patients are planned to take Jian-Pi-An-Tai formula for 5 weeks.

The control group: conventional western medicine after embryo transplantation.

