### 2.6. Outcome measures

#### 2.6.1. Primary outcome measures

Embryo implantation rate: number of embryos implanted/total number of embryos transferred * 100%. Blood sampling test of β-HCG will be taken on the 8th and 10th days after embryo transfer. Positive results can be determined as successful embryo implantation.Clinical pregnancy rate: number of clinical pregnancies/number of implanted embryos * 100%. Doppler ultrasound will be taken on the 5th week after embryo transfer. Gestational sac and fetal heart beat can be determined as successful clinical pregnancy.Persistent pregnancy rate: number of cycles of continuous pregnancy/number of embryos implanted * 100%. Doppler ultrasound will be taken on the 12th week after embryo transfer. Existence of fetal heart beat can be determined as successful persistent pregnancy.

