### 2.9. Statistical analysis

The statistical analysis of this study will be conducted by statisticians of the Zhejiang Chinese Medical University. Software packages SPSS 23.0 and SAS 9.3 will be used for statistical analysis. All statistical tests will be conducted by 2-sided tests and *P* values less than .05 are considered statistically significant. The description of quantitative indicators will calculate the number of cases, mean, standard deviation, median, minimum and maximum. Classification indicators are described by the number of cases and percentages of each category. Normally distributed data is represented by mean ± standard deviation, and non-normally distributed data is represented by median and interquartile range. Comparisons between groups of measurement data will be conducted by using independent sample *t* test, and within group differences will be tested with paired *t* test. Differences between groups of numeration data will be assessed with chi-square test.

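### The weekly hormone comparison, read literally, is confined to women selected by a primary outcome read after treatment has begun, and non-normal data are described by medians but compared only by t test

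*Protocol article*

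**What the plan says.** Section 2.6.2.2 of the protocol article makes β-HCG, E2 and P a secondary outcome whose "levels will be measured once a week after embryo implantation". It adds that "additional tests should be conducted at any time according to the clinical needs". It gives no end date for the series.

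Section 2.6.1 states how implantation is recognised: "Blood sampling test of β-HCG will be taken on the 8th and 10th days after embryo transfer", and "Positive results can be determined as successful embryo implantation". The implantation rate is the first primary outcome.

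Section 2.5 places treatment after transfer: "The treatment group: conventional western medicine after embryo transplantation combined with Jian-Pi-An-Tai formula". The planned course is 5 weeks.

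Section 2.9 says that "non-normally distributed data is represented by median and interquartile range". For testing, it says "Comparisons between groups of measurement data will be conducted by using independent sample" *t* tests, with paired *t* tests within groups. It names no other method for comparing a continuous outcome between arms.

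**The concern.** Implantation status is read after randomisation and after the start of treatment, and it is what the formula is meant to change. If the weekly series begins only once a woman has implanted, those who do not implant contribute nothing to it, and the women left in each arm need not be alike.

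Suppose the formula works by letting less viable embryos implant. The treated arm then contains more marginal pregnancies, and its average hormone level can fall although the formula does nothing to the hormone. A real benefit on the primary outcome could then appear as an unfavourable result on a secondary one.

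The second matter is smaller. Section 2.9 allows for non-normal data when describing results but not when testing them, so medians could be printed beside a p-value that compares means.

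**Working it through.** **1. Who is in the comparison.** Three sections, side by side:

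- Section 2.5: treatment follows transfer.
- Section 2.6.1: implantation means a positive β-HCG from the day-8 and day-10 samples, counted from transfer.
- Section 2.6.2.2: the weekly hormone series follows implantation.

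In section 2.6.1 transfer and implantation are separate events. With that meaning carried over, entry to the weekly series depends on a result obtained after treatment has begun. The day-8 and day-10 β-HCG is timed from transfer and does not have this problem.

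**2. How large the selection effect could be.** The document gives no design figure for the hormone outcome, so there is none to reproduce. It also gives no hormone SD and no implantation rates. The following is a range under assumptions.

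*Inputs from section 2.8:* 180 participants in 2 groups and 10% drop-out. Equal arms are assumed, giving 90 × 0.9 = 81 evaluable per arm. The rates 86.2% and 54.2% are response rates for an endpoint that the section does not define. They are borrowed here only as an extreme.

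*Assumed model:* each woman has a latent embryo viability V ~ N(0,1). She implants if V exceeds a threshold set so that a proportion p of the arm implants. Log hormone has correlation ρ with V, and treatment has no effect on the hormone. A higher implantation rate means a lower threshold.

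*Formulas:* with c = Φ⁻¹(1 − p), the mean of V among implanters is λ(p) = φ(c)/p. The spurious shift, in SDs of log hormone before selection, is ρ[λ(p_T) − λ(p_C)]. The variance of V among implanters is v = 1 + cλ − λ², so their hormone variance is 1 − ρ² + ρ²v. The two arms' variances are averaged, and the standard error uses 81·p_T and 81·p_C women.

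*Extreme case, 86.2% vs 54.2%:* λ = 0.256 and 0.732, a difference of -0.476. About 70 women (81 × 0.862) are compared with 44 (81 × 0.542).

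*Modest case, 60% vs 50%:* λ = 0.644 and 0.798, a difference of -0.154. About 49 women are compared with 41.

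| Implanting | ρ | Shift (SD) | False rejection at two-sided 5% |
|---|---|---|---|
| 60% vs 50% | 0.3 | -0.05 | 5.6% |
| 60% vs 50% | 0.5 | -0.08 | 6.8% |
| 60% vs 50% | 0.7 | -0.11 | 9.3% |
| 86.2% vs 54.2% | 0.3 | -0.14 | 12% |
| 86.2% vs 54.2% | 0.5 | -0.24 | 26% |
| 86.2% vs 54.2% | 0.7 | -0.33 | 51% |

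The shift is proportional to ρ and grows with the gap in implantation rates. If the rates are equal it is zero in this model.

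**3. What the t test costs if a hormone is skewed.** Log-normal data were simulated (20,000 runs, 44 and 81 women per arm), with the effect set so that a t test on the log scale has about 80% power. The large-sample efficiency of the raw test relative to the log test is s²/(exp(s²) − 1), with s² = ln(1 + CV²). At CV 1.0, for example, s² = 0.693 and the efficiency is 0.693/(2 − 1) = 0.69.

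| Assumed CV | Relative efficiency | Power, raw t test |
|---|---|---|
| 0.5 | 0.89 | 75% |
| 0.8 | 0.77 | 69% |
| 1.0 | 0.69 | 66-67% |
| 1.5 | 0.52 | 57-58% |

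The Mann-Whitney test (4,000 runs) kept about 77-78%. The type I error of the raw t test was 4.2-4.9%.

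**The case against.** The strongest reply is that implantation in section 2.6.2.2 may be loose wording for transfer. The article also uses transplantation in section 2.5, so its terms are not uniform. If transfer is meant, the selection argument falls away. That stands as a possibility, but section 2.6.1 gives the two words different meanings, so section 2.6.2.2 needs clarifying either way.

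It is also fair that the article is condensed and that an analysis plan not shown could specify a transformation, a rank test or a repeated-measures model. Silence on these is not an error. What remains is narrower: section 2.9 foresees non-normal data, changes the summary statistic, and still names only one between-group test.

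A reader might infer more than the document supports:

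- *That all hormone data are confined to implanters.* They are not: the day-8 and day-10 β-HCG is timed from transfer.
- *That unscheduled samples enter the outcome, mainly from women with complications.* Section 2.6.2.2 allows extra tests for clinical reasons. It does not say that they are analysed or who would have them.
- *That each hormone will be tested every week, with a resulting multiplicity problem.* The series has no stated end and section 2.9 prescribes no weekly tests, so there is nothing to count.
- *That β-HCG is known to be skewed, or that the t test is invalid.* The document says nothing about hormone distributions. Under the assumed skewness the loss is in power, and type I error holds.

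**Conclusion.** The concern holds in a limited form. As written, sections 2.5, 2.6.1 and 2.6.2.2 together make the weekly hormone series a comparison of women selected by a primary outcome read after treatment has begun. It is therefore not a randomised comparison.

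The possible bias is small for a modest gap in implantation and material only at the extreme, where it could produce a false finding in 12% to 51% of trials. These figures rest on the latent-viability model, the assumed correlations, equal arms and borrowed implantation rates. They show a plausible range and do not predict this trial's result.

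The mismatch in section 2.9 is the lesser point. Its cost is about 5 to 23 percentage points of power for an assumed CV of 0.5 to 1.5, and it does not threaten validity. Both matters concern a secondary outcome, but correcting them costs almost nothing.

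**What to change.** 1. Reconcile the time origin in section 2.6.2.2 with the terms of section 2.6.1, and state which women contribute to the weekly series.
2. If implantation is meant, label the weekly comparison of β-HCG, E2 and P as descriptive among women who implanted, and draw no conclusion on efficacy or harm from it. If transfer is meant, say so, and include all randomised women.
3. For a comparison of all randomised women, use the day-8 and day-10 β-HCG, which is already planned. State its limits: it overlaps with the implantation outcome, and it does not cover E2 or P.
4. In section 2.9, compare non-normal continuous outcomes on the log scale, reported as a ratio of geometric means, or by a rank test. Use scheduled samples only. Clinically indicated tests can continue outside the comparison.

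The cost is a few sentences and no additional blood samples if implantation is meant. The downside is that the weekly hormone result then becomes descriptive and can no longer support an efficacy claim.

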### 2.7. Safety evaluation

Blood sampling test of liver function and blood routine examination will be conducted before, during, and after treatment of Jian-Pi-An-Tai formula.

### 2.8. Sample size calculation

The number of participants is capable to detecting according to the results of the previous study (overall response rate of was 86.2% in the treatment group; 54.2% in the control group) with an alpha error of 0.05 and beta error of 0.2. Considering the 10% drop-out rates, the sample will be composed of 180 participants randomized into 2 groups.

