## Abstract

**Methods::**

This randomized controlled trial (RCT) will be carried out in Hangzhou TCM Hospital Affiliated to Zhejiang Chinese Medical University planning to recruit 180 infertile patients undergoing IVF-ET with the type of deficiency of both the spleen and kidney. The control group will be treated by conventional western medicine and the treatment group will use conventional western medicine plus Jian-Pi-An-Tai formula. The primary outcomes will include Embryo implantation rate, Clinical pregnancy rate, Persistent pregnancy rate; and the secondary outcomes will include TCM symptom score and reproductive hormones. Safety evaluation will be recorded during the whole study. All data in this RCT will be analyzed by SPSS 23.0 software. This study has been approved by the Research Ethics Committee of the Hangzhou TCM Hospital Affiliated to Zhejiang Chinese Medical University (2022KY130).

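### The sample size of 180 does not follow from the inputs in section 2.8 (about 70 to 84), and the response rate behind it is undefined and not a trial outcome, so 80% power is not established for any primary outcome

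*Protocol article*

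**What the plan says.** Section 2.8 takes its two rates from a previous study: "overall response rate of was 86.2% in the treatment group; 54.2% in the control group". It sets the error rates "with an alpha error of 0.05 and beta error of 0.2" and concludes: "Considering the 10% drop-out rates, the sample will be composed of 180 participants randomized into 2 groups". The allocation ratio is not given.

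Section 2.9 supplies the rest of the design: "All statistical tests will be conducted by 2-sided tests", and for categorical data, "Differences between groups of numeration data will be assessed with chi-square test".

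The abstract lists the outcomes to which the sample size should relate: "The primary outcomes will include Embryo implantation rate, Clinical pregnancy rate, Persistent pregnancy rate". Section 2.6.1 defines these three as ratios over embryos: the first over embryos transferred, the other two over embryos implanted. The secondary outcomes in section 2.6.2 are a TCM symptom score and reproductive hormones. No overall response rate is listed or defined in any of these sections, and section 2.8 does not say which outcome it stands for.

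**The concern.** There are two separate problems in section 2.8.

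- **Arithmetic.** A 32-point difference between proportions is very large and needs few patients at 80% power. A total of 180 looks far too big for it. Because the article prints both the inputs and the result, this is a mismatch on the page and not a detail left to a fuller document.
- **Endpoint.** The rates belong to a quantity that this trial does not list as an outcome. Even a correct calculation on them would not describe the power of the comparisons that will be made.

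At stake is how the result is read. Someone relying on section 2.8 would take the trial to have at least 80% power for its pregnancy outcomes. A non-significant result could then pass as good evidence of no benefit, although the protocol does not say what difference in those outcomes 180 women could detect.

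**Working it through.** **Inputs.** From section 2.8: p1 = 0.862, p2 = 0.542, difference d = 0.320, alpha 0.05, power 0.80, drop-out 10%, total 180. From section 2.9: two-sided tests, chi-square. Assumed: 1:1 allocation.

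**Step 1: reproduce the plan's figure.** The usual formula with pooled variance under the null is

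n per arm = [1.96 × √(2·p̄·(1 − p̄)) + 0.8416 × √(p1(1 − p1) + p2(1 − p2))]² / d²

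- p̄ = (0.862 + 0.542)/2 = 0.702, so 2 × 0.702 × 0.298 = 0.4184, and 1.96 × √0.4184 = 1.268.
- 0.862 × 0.138 + 0.542 × 0.458 = 0.1190 + 0.2482 = 0.3672, and 0.8416 × √0.3672 = 0.510.
- n = (1.268 + 0.510)² / 0.1024 = 30.9, so 31 per arm.
- With continuity correction: n' = (30.86/4) × [1 + √(1 + 4/(30.86 × 0.32))]² = 36.8, so 37 per arm.

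Drop-out: 31/0.9 = 34.4, so 35 per arm and **70 in total**. With correction, 37/0.9 = 41.1, so 42 per arm and **84 in total**. The stated figure is 180.

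**Step 2: look for a reading that gives 180.** Totals after 10% drop-out:

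| Variant | Total | With continuity correction |
|---|---|---|
| Two-sided 0.05, 80% power | 70 | 84 |
| One-sided 0.05, 80% power | 56 | 70 |
| Two-sided, unpooled variance | about 63 | – |
| Two-sided, arcsine | about 66 | – |
| Two-sided, 2:1 or 3:1 allocation | about 73 to 98 | (covered by the range) |
| Two-sided 0.05, 90% power | 92 | 106 |
| Two-sided 0.05/3, 80% power | 94 | 108 |

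Nothing at the stated alpha and power exceeds about 98. Totals near 180 appear only with settings that the article does not state. For example, two-sided 0.05/3 with 98% power gives 172, or 186 with correction.

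**Step 3: power at the stated size.** 180 × 0.9 = 162 evaluable, or 81 per arm.

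- Standard error under the null: √(0.4184/81) = 0.0719. Under the alternative: √(0.3672/81) = 0.0673.
- z = (0.320 − 1.96 × 0.0719)/0.0673 = 2.66, so power is **99.6%**. With 90 per arm it is 99.8%.

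**Step 4: what 162 evaluable women could detect (illustration only).** The protocol gives no expected rate for any primary outcome, so control rates of 30% to 60% are assumed. The setting is one outcome, one result per woman, two-sided 5%, 81 per arm.

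| Control rate | Difference with 80% power | Power for 15 points | Power for 10 points |
|---|---|---|---|
| 30% | 21.5 points | 50% | 26% |
| 40% | about 22 points | 48% | 25% |
| 50% | about 21 points | 49% | 25% |
| 60% | about 20 points | 53% | 26% |

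Check on one example: 40% against 62% with 81 per arm has 80.6% power.

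**The case against.** **The error is on the generous side.** The trial enrols more than twice what its inputs require, so the mismatch cannot by itself make the trial too small. This is correct. Only the missing link to an outcome leaves the power for the pregnancy outcomes open.

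**Does any primary outcome fall short of 80% power?** A reader might infer that none of the three reaches it. The document does not support that. It gives no expected rates for these outcomes. A true per-woman difference of about 20 to 22 points or more would reach 80% under the assumed control rates, and if the 32-point difference applied to a per-woman outcome, power would be over 99%. The power is unestablished, not shown to be inadequate.

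**The response rate may be a pregnancy-type success rate under another name.** The previous study is not shown, so this cannot be excluded. What can be said is that the rate is undefined and not tied to a listed outcome, not that it is irrelevant. The fix leaves room for the authors to define it.

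**The illustration is per woman, but the protocol counts embryos.** This also stands. Section 2.3.1 specifies two embryos per transfer, so 81 women per arm would contribute 162 transferred embryos, with correlation within a woman. For implantation, a 15-point difference with control rates of 30% to 50% then has about 77% to 80% power if the two embryos behave independently, about 60% to 63% at an intra-woman correlation of 0.5, and about 48% to 50% if they always share the same fate. The 20 to 22 points should therefore not be read as the detectable difference for the outcomes as section 2.6.1 now defines them.

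**A detectable difference worked back from a fixed 180 is no real justification.** In part this is fair. It is still a true statement about the trial, which the present text is not.

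**Conclusion.** The point holds in two parts.

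1. The stated inputs lead to about 70 women (84 with continuity correction), and no standard variant at the stated alpha and power leads to 180. The described design has about 99.6% power for its stated difference, not 80%. This rests on 1:1 allocation and the two-sided tests of section 2.9. Neither one-sided testing nor 2:1 or 3:1 allocation closes the gap.
2. The response rate used is undefined and is neither a primary nor a secondary outcome. Section 2.8 therefore does not establish 80% power for implantation, clinical pregnancy or persistent pregnancy.

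It does not follow that the trial is underpowered. The figures of 20 to 22 points for 80% power, 48% to 53% power for 15 points and 25% to 26% for 10 points rest on assumed control rates of 30% to 60%, one result per woman and a single outcome tested at two-sided 5%. They show the order of magnitude and are not estimates for this trial. The section is wrong as written and should be corrected, because it is the only justification given for the trial's size.

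**What to change.** Keep 180 and rewrite section 2.8 for one named primary outcome analysed per woman randomised. State the allocation ratio, the expected control rate with its source, and the difference that 162 evaluable women can detect with 80% power at two-sided 5%. If persistent pregnancy were chosen and a control rate of 40% could be supported, the text could read: *With 180 women randomised 1:1 and 10% drop-out, 162 evaluable women (81 per arm) give 80% power at two-sided 5% to detect a difference of about 22 percentage points in persistent pregnancy per woman randomised, for example 40% against 62%.* The 40% is a placeholder for the authors' own figure.

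Remove the 86.2% and 54.2% as the basis for 180, unless the response rate is defined and shown to be one of the trial's outcomes. In that case, state the power actually achieved (over 99%) in place of 80%.

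A per-woman statement must match the outcome definition, so the denominator of the chosen outcome in section 2.6.1 has to be aligned with it. If an embryo-based denominator is kept, the detectable difference has to be calculated on that basis, allowing for two embryos per woman.

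Cost: no extra patients and no change to 180. The work is wording in section 2.8 and the matching definition. The downside is that the stated property becomes less favourable: a detectable difference of perhaps 20 points or more has to be printed and defended as plausible.

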### 2.9. Statistical analysis

The statistical analysis of this study will be conducted by statisticians of the Zhejiang Chinese Medical University. Software packages SPSS 23.0 and SAS 9.3 will be used for statistical analysis. All statistical tests will be conducted by 2-sided tests and *P* values less than .05 are considered statistically significant. The description of quantitative indicators will calculate the number of cases, mean, standard deviation, median, minimum and maximum. Classification indicators are described by the number of cases and percentages of each category. Normally distributed data is represented by mean ± standard deviation, and non-normally distributed data is represented by median and interquartile range. Comparisons between groups of measurement data will be conducted by using independent sample *t* test, and within group differences will be tested with paired *t* test. Differences between groups of numeration data will be assessed with chi-square test.

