## 2. Methods

### 2.1. Trial design

This study is a protocol for a randomized, non-blinded, controlled clinical trial. A total of 180 infertile patients with the type of Deficiency of both spleen and kidney will be conducted according to the flow diagram and will last for near 2 years, scheduled to start from January 2023 (Fig. 1).

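### The TCM symptom score has a baseline, but section 2.9 names no baseline adjustment and adds within-arm paired t tests not labelled descriptive: a free improvement

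*Protocol article*

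**What the plan says.** Section 2.6.2.1 of the protocol article lists the TCM symptom score as a secondary outcome and gives two measurement times: "The form of TCM symptom will be measured at the baseline, after 5 weeks of treatment".

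Section 2.9 does not name the score, but its rule for measurement data covers it. The rule has two parts. Between arms: "Comparisons between groups of measurement data will be conducted by using independent sample" t tests. Within arms: "within group differences will be tested with paired" t tests. No baseline covariate or model is named. The section does not say whether the between-arm test uses the week-5 score or the change from baseline.

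The same section states that "All statistical tests will be conducted by 2-sided tests" and sets one significance threshold, P < .05, for all of them. Nothing marks the paired tests as descriptive.

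Section 2.1 describes the design: "This study is a protocol for a randomized, non-blinded, controlled clinical trial".

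**The concern.** Two matters are involved, of different kinds.

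The first is precision. A baseline score is collected for every woman. If it predicts the week-5 score, a between-arm analysis that does not condition on it leaves explainable variation in the error term and gives a wider interval than necessary.

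The second is interpretation. A paired test within one arm asks whether that arm changed, not whether it changed more than the other. Women are enrolled with a TCM syndrome diagnosis (section 2.3.1), and neither they nor their doctors are blinded. Some improvement in both arms without any formula effect is therefore plausible, through regression to the mean, expectation or natural course, although the document does not give its size. If the formula arm then crosses P < .05 and the control arm does not, the pair of results is easily read as evidence of benefit, although the difference between the arms has not been shown to be significant. What is at stake is one secondary outcome and how it is reported.

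**Working it through.** **The plan's own figure.** The document gives no power or precision figure for the symptom score. Its only sample-size figure is the total of 180 in section 2.8, from "overall response rate of was 86.2% in the treatment group; 54.2% in the control group" and "with an alpha error of 0.05 and beta error of 0.2". With p1 = 0.862, p2 = 0.542 and mean 0.702, the two-sided pooled formula gives

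n = [1.96 × √(2 × 0.702 × 0.298) + 0.842 × √(0.862 × 0.138 + 0.542 × 0.458)]² / 0.320² ≈ 31 per arm.

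This becomes 31/0.9, rounded up to 35 per arm with 10% dropout, or 70 in total (84 with continuity correction). The stated 180 is not reproduced. That is a separate matter. Here 180 serves only to fix the arm size.

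**Inputs.**
- Arm size: 180 in two groups with 10% dropout (section 2.8). Equal allocation is assumed: 90 per arm, 90 × 0.9 = 81 evaluable.
- Two-sided 5% tests (section 2.9).
- Correlation r between baseline and week-5 score: not in the document; assumed 0.3, 0.5 and 0.7.
- Equal SD at both times and in both arms: assumed. Normal approximation throughout.

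**Step 1, precision.** Relative to a week-5 t test (variance 1), a change-score t test has variance 2(1 − r) and ANCOVA has 1 − r². ANCOVA relative to the change score is therefore (1 − r²)/[2(1 − r)] = (1 + r)/2. The equivalent arm size for a week-5 t test is 81/(1 − r²).

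| r | ANCOVA vs week-5 t test | ANCOVA vs change-score t test | Equivalent n per arm |
|---|---|---|---|
| 0.3 | 0.91 (9% lower) | 0.65 (35% lower) | 81/0.91 ≈ 89 |
| 0.5 | 0.75 (25% lower) | 0.75 (25% lower) | 81/0.75 = 108 |
| 0.7 | 0.51 (49% lower) | 0.85 (15% lower) | 81/0.51 ≈ 159 |

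In terms of power, the effect a week-5 t test detects with 80% power at 81 per arm is (1.96 + 0.842) × √(2/81) = 0.44 SD. For that effect:

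| r | Week-5 t test | Change-score t test | ANCOVA |
|---|---|---|---|
| 0.3 | 80.0% | 65.8% | 83.6% |
| 0.5 | 80.0% | 80.0% | 89.9% |
| 0.7 | 80.0% | 95.1% | 97.5% |

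ANCOVA is the most precise at each r shown, whichever t test is meant.

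**Step 2, the paired tests.** Suppose there is no treatment effect and both arms improve by δ (in SD units). Each paired test shows significant improvement with probability p = 1 − Φ(1.96 − δ√81/√[2(1 − r)]). The arms are independent, so the chance that the formula arm is significant and the control arm is not is p(1 − p). Example: δ = 0.2 and r = 0.5 give 0.2 × 9/1 = 1.8, p = 1 − Φ(0.16) = 0.436, and 0.436 × 0.564 = 0.246.

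| δ (assumed) | r = 0.3 | r = 0.5 | r = 0.7 |
|---|---|---|---|
| 0.1 | 10.2% | 12.4% | 16.7% |
| 0.2 | 22.1% | 24.6% | 23.0% |
| 0.3 | 23.4% | 17.7% | 6.0% |
| 0.5 | 3.2% | 0.6% | 0.0% |

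The expression p(1 − p) cannot exceed 0.25, reached at p = 0.5. For comparison, the between-arm two-sided 5% test falsely favours the formula in 2.5% of trials.

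**The case against.** The strongest reply is that nothing here is an error. Under randomisation the unadjusted t test is unbiased and keeps its type I error rate, and chance baseline imbalance is already reflected in its standard error. A between-arm test is planned in the same sentence as the paired tests, so between-arm evidence will exist, and no passage says that paired tests will support an efficacy claim. Covariate adjustment is often left to a statistical analysis plan, which is not shown. All of this stands except the last step: section 2.9 does not leave the matter open but names both tests, and places the paired tests under the same significance rule.

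A reader might go further than the document allows in four ways.
- That the between-arm test disregards baseline altogether. The text does not say so; a change-score test would use it. The gain from ANCOVA then has a different size and falls, rather than rises, with r.
- That the plan would claim benefit from within-arm results. It does not; this is a risk of misreading.
- That discordant paired tests would mislead in half of all trials. A figure of 2p(1 − p) = 50% is the maximum, needs exactly 50% power in each arm, and counts trials where only the control arm is significant, which no one would read as benefit. The relevant share is at most 25%, and is close to zero if both arms improve by 0.5 SD and r is 0.5 or more.
- That the pregnancy outcomes are affected, or should also be covariate-adjusted. They are rates, for which section 2.9 uses chi-square tests, and nothing in this point bears on them.

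**Conclusion.** The point holds as a free improvement, not as a flaw that invalidates an analysis. The planned between-arm test of the symptom score is valid. What is lost is precision: 9% to 49% of the variance against a week-5 t test, or 35% to 15% against a change-score t test, as r goes from 0.3 to 0.7. The paired tests do not estimate the formula's effect, and if read as though they did, could suggest benefit in about 0% to 25% of trials with no treatment effect.

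These figures rest on assumed correlations, assumed common improvements of 0.1 to 0.5 SD, equal SDs and 81 evaluable women per arm. The direction of the precision result does not depend on the exact r in that range; the size of both results does.

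**What to change.** In section 2.9, state that the week-5 TCM symptom score will be compared between arms by ANCOVA with arm and baseline score as terms, reporting the adjusted mean difference with its 95% CI. This also removes the ambiguity over week-5 score or change, since with baseline in the model both give the same arm difference. State that within-arm change will be summarised descriptively, without p-values, and remove the paired t tests.

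The cost is about one sentence of analysis text. Both measurements are already scheduled, and neither sample size nor visits change.
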